**4.0 Research Design**

The proposed research design includes the utilization of randomized controlled trial methods in order to evaluate integrated health and housing services. The project involves two sub-populations of homeless individuals, characterized by different eligibility criteria: one group with “high needs” and a second group with “moderate needs”. The project thus consists of two related but distinct RCTs which differ with regard to the severity of participants’ needs, the number of intervention arms, and the type of intervention services. Despite these differences, many of the major methodological features of each RCT will be the same. These include: participant recruitment and retention strategies, tests and measures of outcomes of interest, study hypotheses, and plans for data analysis. In addition, both RCTs incorporate qualitative and quantitative methods along with the secondary analysis of administrative data.

Participants with high needs will be randomized to one of two *Housing First* program variations (Scattered-site + ACT or Congregate + ACT\*) or to a Treatment as Usual (TAU) group (see Figure 2). Participant choice will be maximized in all study conditions, and all study participants who are randomized to an intervention group will receive some form of low-barrier housing as well as intensive support services. Moderate need participants will be randomized to one of two groups, an intervention (Scattered-site + ICM) or TAU group. Please see Section 4.4 for details on the housing and support interventions as well as the TAU group.

[figure not shown]

\*Intensive treatment services will be integrated into the congregate housing condition. In the event that an ACT team cannot be developed in this condition, the service component will consist of a comparable range and intensity of services.

All study participants will be followed and re-interviewed every 6 months for a period of 2 years from baseline. A field office will be established to facilitate tracking and interviewing of participants. The field office will be utilized as a confidential location for conducting follow-up interviews as well as a place where participants can ask questions about the project, their next interview (e.g., date, time, etc.), and update their contact information.

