## 4.3 Recruitment

Recruitment will rely on referral from a variety of sources (e.g., Community Court; mental health and addiction services; Emergency Departments; shelters) and outreach. Outreach workers and service providers will be asked to inform homeless people about the project. Recruitment materials (e.g., posters, brochures) will be distributed in the community and displayed in organizations that serve the target population (e.g., soup kitchens, shelters, drop-in centres, health clinics, etc.). Recruitment will also rely on word-of-mouth among friends and associates (“snowballing”). The research team will conduct information sessions with community organizations and professionals who serve the target population to inform them about the project and gain support. Specific organizations that target women and ethnic minorities will be contacted to encourage diversity in the sample. Screening will be conducted via laptop computer within community agencies and the field office will be used for baseline and follow-up interviewing.

Recruitment to the full sample is estimated to take 18 months (1 year following a 6 month implementation phase). However, two potential issues related to our ability to recruit participants may extend this period: (1) the randomization process, and (2) compliance with the research protocol. Participants may perceive randomization to intervention and comparison groups as being ‘good’ or ‘bad,’ respectively, possibly leading to refusal to participate. Further, some participants may be hesitant to comply with the rigors of the protocol.

**Screening and Baseline Evaluation:** The screening process will consist of two primary steps:

1. **Pre-Screening:** Due to the nature of chronic homelessness in the DTES, it is likely that most individuals will have an addiction and/or mental illness (Goldner et al., 2007). Thus, the basic criteria needed to conduct pre-screening will be age 19 years or older, competence to sign the screening consent form, proficiency in spoken English, and *absolute homelessness* or *precarious housing* (as defined by the MHCC).

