**Plan to Secure a Housing Portfolio:** A challenge for the Vancouver site will be in securing sufficient scattered-site units during the recruitment phase (Sept. 2009-Aug. 2010) which coincides with the 2010 Winter Olympics. Strategies to address this challenge will be developed by MPA in collaboration with the Project Team, BC Housing, the City of Vancouver and other formal and informal partners. The following actions will be taken to secure an adequate housing portfolio for the project:

- Hire a full-time property and portfolio Manager under the direction of the Program Director;
- Work with BC Housing, the City of Vancouver and other non-profit social housing providers to secure housing units;
- Focus on portfolio development and relationship-building with landlords; build on existing relationships and support landlords towards successful tenancies; facilitate landlord round-tables and education forums, and form associations with landlord groups;
- Develop a dispute resolution process for landlords, and respond quickly to incidents via investigation, mediation and resolution;
- Engage people with lived experience in landlord education and relations;
- Develop procedures and checklists to ensure housing quality; monitor landlords' care and attention to clients; respect for tenancy agreements; etc.
- Support both ACT and ICM providers with immediate access to housing for clients; maintain ongoing communication with case workers and appropriate intervention with landlords;
- Liaise with Ministry of Human Resources regarding damage deposits and rent as necessary;
- Develop memos of understanding regarding roles and responsibilities with ACT and ICM leads.

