##### 4.6.2.1 Surveys and Questionnaires

The survey instruments consist of previously validated measures recommended by the National Project Team. We have also proposed a number of additional relevant measures. Copies of instruments are presented in Addendum B. Please see Appendix 5.0 for a summary of the timing of administration.

Housing status over the preceding 6 months will be determined at baseline and at the time of each follow-up interview using the Housing Timeline Follow-Back Calendar (HTFBC). The primary outcome variable will be housing status at the time of the 2 year follow-up interview, defined as being either: (1) Homeless, or (2) Stable Housing (living for a continuous period of at least 90 days in a house,

 The SOS is based on the core of the modified Overt Aggression Scale (see Addendum for a copy of this instrument).

apartment, SRO hotel, rooming house, or any other place of one's own for which one pays rent; Ontario MCFS, 2004). Other outcome variables to be derived from the HTFBC will include: (1) housing status at each follow-up period; (2) number of housing transitions over the previous 6 months; (3) number of nights spent homeless over the previous 6 months. The Housing Quality Score will be used to determine self-reported quality of current living conditions in terms of comfort, safety, spaciousness, privacy, friendliness and overall quality.

Demographic characteristics will be collected using subsections of the Community Mental Health Evaluation Initiative (CMEI). Quality of life will be assessed using two instruments: (1) The Quality of Life for Homeless & Hard to House Individuals (QOLHHI) Instrument (Hubley & Palepu, in preparation); and (2) the EuroQol (EQ5D), a standardized health-related quality of life instrument that generates a composite score reflecting the preference value associated with a given health state, and a global rating of current health using a visual analog scale. General functioning will be assessed using the Multnomah Community Ability Scale (MCAS). Resiliency will be assessed using the 3-item Sense of Coherence Scale. Vocational outcomes will be assessed using a timeline follow-back interview from the Montreal IPS study (indicated by MHCC), which examines work status and various details of work (e.g., setting, timing, hours, compensation, etc.).

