### **5.1 Quantitative Data**

**Risks to subjects.** *Human subjects involvement.* Baseline interviews will be conducted with 500 participants with four follow-up interviews over a period of 2 years. All participants will be of legal adult status. Potential risks associated with the interviews are embarrassment and discomfort from discussing matters such as personal mental health problems or drug use. However, past research with similar surveys indicates that such risk is minimal. Further, these potential risks can be minimized by training interviewers carefully and by assuring subjects that interviews will be conducted in private. Another potential risk involves updating contact information at each follow-up interview with respondents who had nearly been lost to follow-up. This information is given voluntarily, and respondents will be familiarized with this process.

Within the context of this study, it is expected that the mental health problems and symptoms of both the moderate and high needs groups will diminish over time. Given the target population and the chronic nature of mental illness, it is likely that some individuals will, over time, move between the high and moderate needs group. However, there is a possibility that some individuals in the moderate need group could experience a significant escalation in their symptoms. In this event, the individual's case will be brought forward to an as yet to be determined committee of researchers and service providers, including a physician, in order to evaluate whether or not the individual or others are in significant danger. In the event that the committee determines the individual is a risk to self or others, the individual will be referred for more intensive treatment.

Physical health examinations (PHE) will be completed with a subset (20%) of study participants at baseline and at 24 months following baseline. PHEs will be carried out by qualified physicians who have expertise providing care to homeless and seriously ill urban patients. Participants will have the option of refusing or discontinuing PHEs at any point. The PHE are anticipated to reveal untreated or undertreated health conditions, which may require immediate or urgent treatment. Good clinical practice will govern the follow up and treatment of medical conditions identified in PHEs.

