| Year 2 (Commencing April 1, 2010)                                                                                                                                                               |                                                               |
| Analyze qualitative data from client narrative interviews                                                                                                                                              | Jan. – March 2010                                             |
| Complete qualitative report on Planning & Proposal Development                                                                                                                                         | April 2010                                                    |
| Complete acquisition of housing units and sites 
 
- Scattered-site units (100 additional units)
 
- Congregate units (possible second building)
 
 |                                                               |
| Primary Data Collection #1: Completion of All Baseline Measures (Wave 1)                                                                                                                        | Oct. 2010 (based on 12 months to full sample)          |
| Fidelity Verification ACT, ICM, Housing First                                                                                                                                                          | Sept. 2010                                                    |
| Retrospective Analysis of Linked Administrative Data                                                                                                                                                   | April – July 2010                                             |
| First Annual Housing First & Housing For All Symposium: Envisioning Success                                                                                                                 | July – August 2010                                            |
| Conduct Follow-up (18 month) Personal Narrative Interviewers                                                                                                                                           | July – Nov. 2010                                              |

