| Gather and analyze qualitative data for Implementation Phase                                                                                                                                           | July – Dec. 2010                                              |
| Year 3 (Commencing April 1, 2011)                                                                                                                                                               |                                                               |
| Primary Data Collection #2: Completion of Follow-up Data Collection (Wave 2)                                                                                                                    | April 2011                                             |
| Completion of sample recruitment                                                                                                                                                                       | April 2011                                                    |
| Complete data entry for all baseline measures                                                                                                                                                          | May 2011                                                      |
| Primary Data Collection #3: Completion of Follow-up Data Collection (Wave 3)                                                                                                                    | Oct. 2011                                              |
| Second Annual Housing First & Housing For All Symposium: Lessons Learned                                                                                                                    | July – Aug. 2011                                              |
| Sustainability Planning                                                                                                                                                                                | (ongoing but intensified in end of Year 3 and through Year 4) |
| Year 4 (Commencing April 1, 2012)                                                                                                                                                               |                                                               |

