| Primary Data Collection #4: Completion of Follow-up Data Collection (Wave 4)                                                                                                                    | April 2012                                             |
| Primary Data Collection #5: Completion of Follow-up Data Collection (Wave 5)                                                                                                                    | Oct. 2012                                              |
| Third Annual Housing First & Housing For All Symposium: Preserving What Works                                                                                                               | July – Aug. 2012                                              |
| Analysis and Major Project Report                                                                                                                                                                      | Jan. – April 2013                                             |

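### The workplan carries two incompatible recruitment ends, and the October 2012 date for the 24-month wave fits only the earlier one

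*Protocol*

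**What the plan says.** Section 4.0 sets follow-up per person: "All study participants will be followed and re-interviewed every 6 months for a period of 2 years from baseline". Section 4.6.2.1 ties the endpoint to the end of it: "The primary outcome variable will be housing status at the time of the 2 year follow-up interview". Section 5.1 gives the total: "Baseline interviews will be conducted with 500 participants with four follow-up interviews over a period of 2 years".

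The recruitment dates fall into two groups.

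- **Shorter timeline.** The Wave 1 row in section 9.0 (all baseline measures) is dated October 2010 and described as "based on 12 months to full sample". Section 4.4.1 discusses securing units "during the recruitment phase (Sept. 2009-Aug. 2010").
- **Longer timeline.** The Year 1 recruitment row in section 9.0 runs from September 2009 to March 2011. In Year 3, "Completion of sample recruitment" is dated April 2011 and baseline data entry is complete in May 2011.

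Section 4.3 can be read either way: "Recruitment to the full sample is estimated to take 18 months (1 year following a 6 month implementation phase").

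Waves 2, 3 and 4 are dated April 2011, October 2011 and April 2012. The row "Primary Data Collection #5: Completion of Follow-up Data Collection (Wave 5") is dated October 2012. Analysis and the main report follow in January to April 2013.

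**The concern.** The workplan has the 6-month wave complete in April 2011, the month in which it also has recruitment complete. A participant enrolled that month cannot have given a 6-month interview, so the two sets of rows cannot describe the same trial.

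The conflict reaches the primary outcome. If recruitment followed the longer timeline and fieldwork followed the wave dates, late enrollees would have no 2-year interview when Wave 5 is due to be complete. Section 4.9 reports no power calculation. It relies on arm sizes set by the funder, which are understood to allow for panel attrition. Nothing there shows an allowance for follow-up cut short by the schedule.

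**Working it through.** **Inputs.** Project start 1 April 2009; recruitment start September 2009; recruitment end March or April 2011 (longer timeline); baseline complete October 2010 (shorter timeline); Wave 5 complete October 2012; report January to April 2013 (all section 9.0). Follow-up of 24 months from baseline (section 4.0). Sample of 500 (section 5.1).

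**1. Reproduce the plan's wave dates.** Wave k completion = baseline completion + 6 × (k − 1) months. From October 2010 this gives April 2011, October 2011, April 2012 and October 2012. All four stated dates match, so the wave schedule is built on the shorter timeline.

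**2. Apply the longer timeline.** March 2011 + 24 months = March 2013; April 2011 + 24 months = April 2013. The last 24-month interviews fall five to six months after October 2012 and inside the report window.

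**3. Share short of month 24 at the stated close.** A participant reaches month 24 by 31 October 2012 only if enrolled by 31 October 2010. September 2009 to October 2010 is 14 calendar months. Share = months of recruitment after the cut-off ÷ total months of recruitment, assuming uniform accrual.

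- End of March 2011: (19 − 14)/19 = 5/19 = 26%; 500 × 5/19 = 132.
- End of April 2011: (20 − 14)/20 = 6/20 = 30%; 500 × 6/20 = 150.

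Moving the start, end and close days within the stated months gives about 22% to 37%.

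**4. Sensitivity.** The protocol gives no accrual curve and no data cut, so both were varied.

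| Assumption | Share short of month 24 |
|---|---|
| Accrual falls linearly over 19 months, close end October 2012 | (5+4+3+2+1)/190 = 15/190 = 8% |
| Accrual rises linearly over 19 months, close end October 2012 | (19+18+17+16+15)/190 = 85/190 = 45% |
| Uniform accrual, fieldwork to end December 2012 | 3/19 = 16% to 4/20 = 20% |
| Fieldwork to end April 2013 | 0% |
| Recruitment ends by October 2010 | 0% |

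**5. Section 4.3.** Eighteen months from 1 April 2009 ends about October 2010, which agrees with the Wave 1 row. Eighteen months from September 2009 ends in March 2011, which agrees with the recruitment row. Counting the same 18 months from two starting points would produce both timelines. That is an inference about the cause; the protocol does not say so.

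**6. Narrative interviews, a separate row.** Section 4.6.2.2 puts the second life-story interview 18 months after the first. Section 9.0 starts first interviews in September 2009, so the earliest second interview is due about March 2011. Section 9.0 dates these interviews July to November 2010. November 2010 is only 14 months after September 2009, so the row fails on either timeline.

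**The case against.** A reader might infer that about a quarter of participants cannot reach the primary endpoint. The protocol does not support that, for three reasons.

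- The October 2010 row and section 4.4.1 both describe recruitment of about 12 months, and on that timeline nobody is cut off.
- October 2012 stands in a column of estimated dates. No section sets a data cut or administrative censoring date. Section 4.0 promises everyone 2 years from baseline, and section 4.6.3 puts the active study period at 2009 to 2013. If recruitment ran late, the more natural reading is a late Wave 5 that overlaps the report.
- Uniform accrual is an assumption. Front-loaded accrual shrinks the share.

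Two further inferences also go too far. Nothing suggests that interviews at 18 to 23 months would be counted as month 24. Nor is there a clear route to bias between arms: section 4.3 randomises in blocks within each need group, so a calendar cut-off would fall about equally on the arms.

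It can also be said that this is an application with details still open, and that only workplan dates are at fault. That limits the weight of the point but does not remove it. The rows contradict each other as written, and the plan contains no late Wave 5. Fieldwork to December 2012 would still leave 16% to 20% short under uniform accrual, and fieldwork to April 2013 runs into the report.

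**Conclusion.** The contradiction stands. Section 9.0 contains a recruitment end of October 2010 and one of March or April 2011, and every wave date follows the first. The consequence is conditional. Only if recruitment runs to the later date and Wave 5 closes at the end of October 2012 would participants lack the 24-month outcome: about 26% to 30% (132 to 150 of 500) under uniform accrual, and about 8% to 45% under linearly falling or rising accrual over 19 months. If recruitment ends by October 2010, or fieldwork runs to April 2013, the loss is nil. The endpoint definition and the 2-year follow-up are not themselves in error. The narrative-interview dates are wrong on either timeline, but they concern about 50 qualitative participants and not the primary outcome.

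**What to change.** State one last-randomisation date and make sections 4.4.1 and 9.0 agree with it. Clarify in section 4.3 that the 18 months are counted from project start. Then choose one of two courses.

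- **Keep the wave dates.** End randomisation by 31 October 2010, keep Wave 5 at October 2012, and correct the recruitment, sample-completion and data-entry rows. The cost is a firm cap on the recruitment window.
- **Keep the longer recruitment.** Move Waves 2 to 5 about six months later, with Wave 5 complete in April 2013, and start the 24-month analysis after that. Sections 4.3 and 4.4.1 must then show recruitment running to March or April 2011. The cost is a report about six months later.

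Separately, redate the 18-month narrative interviews so that none falls before about March 2011. All of this is a change of wording and dates, cheap if made before recruitment starts.
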